### Qualitative study component

#### Study population

The study population for the qualitative component will be policymakers (employees of the District Health Office), healthcare providers, allied health practitioners, laboratory technicians, TB patients, parents of child contacts, and adult contacts of TB patients.

#### Methodological approaches

Qualitative data in the form of interviews, focus group discussions, and diarized observation will be collected by the doctoral researcher (TL), assisted by a trained research assistant.

*Semi-structured interviews* will be undertaken with TB patients, parents of child contacts, and adult contacts of TB patients. An interview guide will be developed on the basis of the theoretical frameworks informing this study—the CFIR and RE-AIM—to gain understandings of relevant barriers and facilitators of contact tracing implementation from the perspectives of providers and clients, and to gain information on their experience of participating in the project. TB patients and their contacts may wish to participate in group interviews rather than one-on-one interviews.

*Focus group discussions* with policymakers, healthcare providers, allied health practitioners, and laboratory technicians will be conducted as part of the continuous quality improvement cycles conducted every 3 to 4 months during the 24-month intervention period. Discussion topic guides will be developed, and written notes of these discussions will be taken and analyzed.

*Informal observations and conversations* on contact management will be made at the participating sites, and notes of these de-identified observations, including discussion in a social media platform described below (“WhatsApp™”), will be used for analyses.

Individual written, informed consent to undertake and record interviews and group discussions will be sought. This will be provided in Bahasa Indonesia, or verbally in a relevant Papuan language. If the study participant cannot sign, a thumbprint will be used to signify consent. Parental consent will be sought for interviews of any TB contacts or index cases aged < 18 years, with additional assent from the subject themselves. Purposive sampling with a maximum variation approach will be employed to select participants [44]. Targeted numbers are shown in Table 4. This sample size provides a feasible number likely to provide an adequate range of opinions, expertise, and themes. However, considering issues of qualitative research emergent design and data saturation, these estimated sample sizes may be subject to change.

**Table 4 Tab4:** Qualitative data collection: sample sizes and target populations

Planned sample sizes for qualitative data collection	
Health care providers	15
Allied health staff	3
Policy makers	7
TB patients	25
TB contacts or their parents	25
Considerations in selection of study participants	
Healthcare providers	
Health institution where participant is employed	Primary health care facility, hospital, district health office, local TB NGO, other TB care provider (clinic, private pharmacy)
Experience with TB	< 5 years, ≥ 5 years
Contact with TB patient	Direct contact (e.g., clinicians) or indirect contact (e.g., laboratory workers)
Knowledge and Training	Trained or not trained in child TB management
Sex	Male and female
Ethnicity	Papuan and non-Papuan
Patients and families	
Education	High school, primary school, or minimal/none. Education level in the family measured by asking level of education of each family member and selecting the highest
Occupation	Formal and informal sector measured by asking occupation of the family member in productive age
Number of families living in the same house	Single family Multiple families
Place of living	Timika City, low-land areas, highland areas
Sex	Male and Female
Ethnicity	Papuan and non-Papuan

Qualitative data will be transcribed by study nurses, translated into English prior to analysis, and organized in NVivo qualitative data analysis software (QSR International Pty. Ltd., Version 10, 2014). Interview data will be analyzed using qualitative content analysis. This method allows a focus on selected aspects of meaning instead of opening the data to wide interpretation. This is done systematically by assigning relevant parts of interview contents to a pre-specified coding frame, built from the theoretical frameworks (CFIR, COM-B, and RE-AIM) and grouped into categories and sub-categories. The data collection (interviews, focus group discussions, observations, and interviews) and coding and categorizing process will be continued until saturation is reached, that is, until no additional new meaning can be found. Coding consistency will be assessed by comparing two rounds of coding carried out by independent coders (TL and [name]). When all categories have been generated, cleaned, and revised, the codes will be structured and narrated to answer the research questions. Text matrices will be made to identify differences between sources or co-occurrences between categories [45].

### Process evaluation: Theories and frameworks

Formative evaluation (evaluation done during project development and implementation to improve ongoing activities) is being undertaken using the CFIR [32]. This process commenced during baseline scoping activities to understand the local context including barriers to implementation of the contact management policy and will continue as qualitative data are collected. The CFIR framework is a synthesis of 19 existing implementation theories [31]. It describes five domains which we have interpreted as relevant to this project as follows: (1) *intervention*—activities to support behavior change among policymakers, healthcare providers, and patients to adopt the TB contact management policy; (2) *outer setting*—the financial and sociopolitical environment of Mimika health services; (3) *inner setting*—management issues at participating hospitals and PHC and factors relating to the research funding and governance; (4) *individuals*—people with key roles in the project at the District Health Office, participating PHCs and hospitals, and patients and their families); (5) *implementation process—*how the activities are rolled out (fidelity to the study protocol) and the development of collaborative relationships.

Alongside the CFIR, the theory used to develop the intervention components is the COM-B model [24]. This model posits that the requirements to change behavior are capability, opportunity, and motivation. To provide capability, opportunity, or motivation to change behavior, interventions (such as education and/or incentives) are needed, which must operate within context-specific policy considerations (e.g., legislative factors). Together these three layers—“COM-B,” “intervention functions,” and “policy considerations”—form the Behaviour Change Wheel [24]. Preliminary information obtained during project planning was categorized according to the CFIR domains and mapped against the Behaviour Change Wheel (Table 5). This provides an initial understanding of the main barriers which need to be addressed for successful policy rollout.

**Table 5 Tab5:** Selected examples of barriers and facilitators identified using the CFIR mapped to the BCW

Consolidated Framework for implementation Research (CFIR)		Behaviour Change Wheel (BCW) components									
Domain of CFIR (domains 1 to 4)	Barriers and facilitators identified using CFIR		Education	Persuasion	Incentives	Coercion	Training	Restriction	Environmental structuring	Modeling	Enablement
(1) Individuals	Knowledge about TB contact investigation and preventive therapy	Influencing capability	X	X			X				
(3) Inner setting	Perceived risk of TB transmission during house visit	Influencing capability and motivation	X	X			X		X		
(2) Outer setting	Language barriers	Influencing opportunity							X		X
(3) Inner setting	Availability of isoniazid for children	Influencing opportunity		X					X		X
(2) Outer setting	Distance to patient’s house	Influencing motivation	X	X	X				X		X
(1) Intervention	Duration of treatment	Influencing motivation	X	X	X						
(4) Implementation process	Delay in identifying child contacts	Influencing capability and motivation	X				X		X	X	X

The evaluation framework we selected is RE-AIM (Reach, Effectiveness, Adoption, Implementation, Maintenance) [32]. This provides a way to describe how the project will be implemented and evaluated and why it will be expected to be successful. The RE-AIM model provides a framework to comprehensively measure public health impact of research conducted in real-world settings rather than controlled trial settings [46, 47]. This is highly suited to our pragmatic intervention. The RE-AIM model consists of five dimensions, occurring in a logical sequence: adoption, reach, implementation, effectiveness, maintenance. Only a small proportion of studies address each dimension and use qualitative inquiry to interpret findings, which can lead to more effective research translation [46]. We address each dimension of the RE-AIM model as described in Table 6.

**Table 6 Tab6:** Application of the RE-AIM framework to this project

RE-AIM dimension and operational definition	Plan	Indicators
How will I and the intervention reach the targeted population? Reach is the absolute number or proportion of individuals who are willing to participate in a given initiative.	• Project staff will visit clinics directly and meet with relevant local stakeholders. We already have support and permission from relevant local authorities to undertake the study. • TB staff at the participating health facilities will be trained in workshops and informal on-the-job interactions to undertake the intervention, comprising identifying TB symptoms and asymptomatic TB contacts, referral, education of patients, prescribing, and monitoring. • Project staff will also have direct contact with selected, consenting TB patients and their contacts through referral by clinic staff, for interviews and provision of education.	• Proportion of health providers who participate in the intervention • Uptake of contact investigation among smear sputum positive TB individual • Uptake of preventive therapy among child contact of smear sputum positive TB cases
How do I know my intervention is effective? Effectiveness is the impact of an intervention on outcomes, including potential negative effects, quality of life, and economic outcomes.	• Relevant data will be collected regularly. The listed quantitative outcome measures will demonstrate whether interventions are working • Results of staff interviews will show whether staff have adequate knowledge of the process of contact management, and whether they are satisfied with the project.	• Significant change in the practice of contact investigation and preventive treatment identified using ARIMA model • Number of new TB cases (adult and children) identified from contact investigation • Number of children eligible for preventive therapy identified from contact investigation • Number of eligible children commence on preventive therapy • Adherence to preventive therapy among eligible contacts
How do I develop organizational support to deliver my intervention? Adoption is the absolute number, proportion, and representativeness of settings and intervention agents who are willing to initiate a program.	• This has been achieved already through face-to-face meetings with and endorsement from the Timika Health Authority (Dinas Kesehatan Timika), as well as endorsement of the study protocol by the National TB expert committee. A partnership agreement has been signed with all selected health facilities. • Number of healthcare workers who were trained and actively participated in the program will be measured.	• Health staff perception about the appropriateness, comfort, relative advantage, and credibility of the intervention • Proportion of TB nurses, TB physicians, head of Puskesmas, hospital managements, and district health office staff who are willing to accept, support. and participate in the intervention • The extent of support and participation of TB-related health staff and stakeholders in the contact investigation and preventive therapy program
How do I ensure the intervention is delivered properly? Implementation refers to the intervention agents’ fidelity to the various elements of the intervention’s protocol	• Project staff will directly supervise project implementation. The research team (study nurses working with doctoral researcher) has been well trained and already has a strong background in TB management. • Data checking will be undertaken regularly during the project.	• Fidelity of the intervention • The extent to which the intervention can be carried out in Puskesmas and Hospital • Gap between indigenous and non-indigenous Papuan people in the access and quality of the intervention
How do I incorporate the intervention, so it is delivered over the long-term? Maintenance is the extent to which a program or policy becomes institutionalized or part of the routine organizational practices and policies.	• The use of continuous quality improvement will embed practice locally and sustainably. • Some actions to repair logistic barriers to TB contact tracing (e.g., lack of medication supply) are being overcome early in the study—this effect will be sustained. • Train-the-trainer concepts will be employed to ensure sustainability of knowledge within healthcare centers. • Inclusion of budget for isoniazid prevention therapy and contact investigation in primary care facilities or hospital budgets can also be indicators of program sustainability.	• The extent to which the intervention is institutionalized or maintained within health facility and district health system • Integration of the intervention to the other existing program in health facilities.

*Puskesmas* pusat kesehatan masyarakat (community health center)

### Intervention components

During the 24-month intervention phase, a suite of interventions will be implemented in a staggered way at the five initial participating sites. Activities will be led by the doctoral research student, supported by the study nurses, a “regional research champion” (Indonesian TB expert), and study investigators. Once policy implementation is well embedded, selected healthcare providers at these sites will be invited to participate in train-the-trainer sessions, so they can disseminate information about the policy at the second-tier (follow-up) sites. The two-tiered approach to the intervention will provide a further measure of sustainability, in addition to the 12-month sustainability period. Intensive activities will take place with the five initial participating sites, then healthcare providers at these sites will then be trained (using a “train-the-trainer” approach) to share their knowledge with the seven follow-up sites.

#### Training

Training will be provided by the doctoral research student and Indonesian TB experts, in the form of workshops for healthcare providers from the five primary participating sites, and any additional healthcare providers from other sites who wish to attend (including the follow-up sites). Training sessions will be free of charge and during usual working hours, by arrangement with management at their respective workplaces. The elements of TB contact management policy will be taught, including practical implications and logistics of rolling this out at each clinic. Hands-on training will be provided in the skills required for policy implementation, such as collection of induced sputum samples from those found to have TB symptoms and provision of accurate weight-based dosing of isoniazid. Pre- and post-training tests will be conducted to understand knowledge and measure the effectiveness of training.

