### Model for clinic participation in study implementation

The study will use a two-tiered approach for policy rollout, comprising initial clinics receiving intensive intervention and follow-up clinics receiving less intensive intervention (Fig. 1). The intention is to generate a “ripple effect” from the initial sites out to a wider catchment. Of 23 primary health centers (PHCs) and 5 hospitals in Mimika district, 10 PHCs and four hospitals are authorized to provide TB diagnosis and management, free of charge. Five sites were initially invited to participate based on their TB burden and location. We purposively selected a mix of urban and rural, private and public, and primary and tertiary sites and included those with largest caseloads. All agreed to participate. Characteristics and locations are shown in Table 2 and Fig. 2. The remaining seven PHCs providing TB care in Mimika will be invited to receive a less intensive follow-up intervention.

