**Fig. 1 Fig1:**
[figure not shown]
Conceptual diagram of study implementation. Intensive intervention is delivered at the five initial sites by the research staff. Second-tier intervention is carried out at the seven follow-up sites by staff from the primary sites

**Table 2 Tab2:** Characteristics of study sites and 2017 TB case load at the five initial participating sites

	TB case burden (2017)	Governance	Location	Number of TB nurses	Number of doctors	Number of beds
Hospital 1	228	Private	Rural	3	2	144
Hospital 2	577	Public	Urban	3	2	159
Primary healthcare center 1	47	Public	Rural	3	1	0
Primary healthcare center 2	192	Public	Urban	5	2	20
Primary healthcare center 3	43	Public	Urban	4	1	2

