#### Mentoring and clinical support

Mentoring and clinical support will be provided directly, through face-to-face discussions during site visits and telephone calls via a WhatsApp™ group. The research team will visit study sites at least weekly to ask about program updates, current activities, and challenges and respond to questions related to program implementation. The research team can also be telephoned at any time as needed. Healthcare providers participating in the study at both initial and follow-up sites will be invited to a WhatsApp™ group moderated by the doctoral research student and with access to an Indonesian TB specialist. WhatsApp™ Messenger is the most widely used, freely available communication application in Indonesia, accessible from mobile devices or desktop computers. This will provide a forum for information sharing relevant to the study, and participants will be able to post questions relating to the contact management policy or other aspects of TB care.

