## Discussion

This study proposal addresses key pillars of the End TB strategy, namely “integrated patient-centered care and prevention” (pillar 1) and “research to optimize implementation and impact” (pillar 3) [3], which are currently underimplemented across high-burden settings. While many aspects of this study plan are specifically tailored to the Mimika context, most components are highly relevant to Indonesia as a whole and high-burden, low-resource settings more broadly.

We considered a range of study designs for this intervention. A community cluster randomized trial (either single-phase or stepped-wedge design) could have been employed, but these designs have limitations. Both require significant resources; a cluster randomized trial in this context could be particularly subject to contamination due to the extent of communication between healthcare providers at healthcare facilities and between the district health authority and healthcare facilities, and there would be ethical implications if the international standard of care (IPT) was not implemented at control sites. A stepped-wedge design might not provide adequate time for interventions to have a maximal effect [48]. We chose a design that was pragmatic and replicable. To test sustainability, a maintenance phase has been included, and the two-staged rollout design will provide an indication of whether local staff using existing resources will be effective in promoting policy implementation at follow-up sites.

The rationale for the use of a combination of theoretical frameworks (the CFIR, Behaviour Change Wheel, and RE-AIM) is that the CFIR is an overarching approach explicitly recommended for use in combination with process and impact theories [31]. It provides a systematic approach for articulating barriers to project implementation. The Behaviour Change Wheel is a well-validated way to then ensure that comprehensive responses to these barriers are provided during project implementation. Finally, an evaluation framework is required to report on process and impact, which is provided by the RE-AIM model, in which the investigator team has experience [51]. However, a potential limitation is that the application of such frameworks is open to the interpretation of study investigators, such that findings from different studies using the same frameworks may be difficult to synthesize [52].

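### Follow-up sites also receive research-led training and chat support, so their results cannot show what local staff achieve with existing resources

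*Protocol article*

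**What the plan says.** Three places in the protocol article describe what the second tier is for and who delivers it.

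- Discussion: the two-stage rollout is to give "an indication of whether local staff using existing resources will be effective in promoting policy implementation at follow-up sites".
- Fig. 1 legend: research staff deliver the intensive intervention at the five initial sites, whereas "Second-tier intervention is carried out at the seven follow-up sites by staff from the primary sites".
- Intervention components: "The two-tiered approach to the intervention will provide a further measure of sustainability", offered in addition to the 12-month sustainability period.

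Model for clinic participation in study implementation sets the intensity: "The remaining seven PHCs providing TB care in Mimika will be invited to receive a less intensive follow-up intervention".

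Two of the listed components then reach the follow-up sites directly from the study team.

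- Training: "Training will be provided by the doctoral research student and Indonesian TB experts". The workshops are for the five primary sites and for "any additional healthcare providers from other sites who wish to attend (including the follow-up sites").
- Mentoring and clinical support: "Healthcare providers participating in the study at both initial and follow-up sites will be invited" to a messaging group that the doctoral researcher moderates and that has access to a TB specialist.

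**The concern.** The Discussion intends to draw a conclusion about a mechanism: local staff, with the resources they already have, carry the policy to further clinics. That conclusion matters because the Discussion looks ahead to project upscaling, where the research team would not be present. Research-led workshops and a specialist-backed chat group are supplied by the study. They are neither existing local resources nor work done by primary-site staff. If contact investigation or preventive therapy rises at the follow-up sites, the data as planned cannot show whether the local trainers, the study team or both produced the rise. A district relying on the result could expect train-the-trainer spread to work without support that was in fact present.

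**Working it through.** No sample size, power or event count enters this point, and Table 3 gives estimates for the five primary sites only. The check is to take each component in turn and ask who supplies it and which sites it reaches.

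1. **Train-the-trainer (Intervention components).** Supplied by providers from the initial sites to the seven follow-up sites. This matches the Discussion's claim.
2. **Training workshops (Training).** Supplied by the doctoral researcher and Indonesian TB experts. They reach the five initial sites and any follow-up-site staff who choose to come. The content includes hands-on skills and the logistics of rollout at each clinic. This does not match the claim.
3. **Chat group (Mentoring and clinical support).** Moderated by the doctoral researcher, with a TB specialist available. The invitation covers participating providers at both tiers. This does not match the claim.
4. **Quarterly quality-improvement workshops (Continuous quality improvement).** Described for the five initial sites only, so they are not a source of mixing.
5. **Weekly visits and telephone support (Mentoring and clinical support).** The text refers to study sites without naming a tier. I do not count this either way.

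So two of the components that reach the second tier are study inputs, and one is the local mechanism of interest.

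**Timing.** Data analysis places activities at both initial and follow-up sites inside the 24-month intervention period, while the research team is active. Intervention components starts train-the-trainer only after the policy is well established at the initial sites. The Training section sets no such condition on workshop attendance. A follow-up site may therefore meet the study team before it meets a local trainer.

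**Can the planned data separate the inputs?** Quantitative study design collects data on study-related activities. Table 6 counts healthcare workers trained. The limitations paragraph of the Discussion promises that the timing and nature of activities will be documented. None of these says that exposure will be recorded by follow-up site, or that it will be used when the follow-up-site result is interpreted. Data analysis calls for separate rates at intervention and non-intervention sites, but does not say when a follow-up site counts as one or the other.

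**The case against.** The strongest reply is that the article never presents the second tier as free of study input. It openly calls the package less intensive, Table 1 lists the seven sites as a second implementation phase, and the quality-improvement cycles, described as a cornerstone, are confined to the initial sites. The Discussion promises only an indication. Activities are documented, trained staff are counted, and interviews will explore why practice changed. A condensed article may also leave site-level reporting to a fuller document.

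Much of this stands. A lower-intensity package is a legitimate thing to evaluate, and open workshops and a chat group fit it. But evaluating that package answers a different question from "whether local staff using existing resources will be effective in promoting policy implementation at follow-up sites". Even an indication requires that the named cause can be told apart from study support. The activity records make the repair cheap but do not make it.

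Four stronger readings are tempting and should not be adopted.

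- *A study objective cannot be answered.* The Background's objective and the listed outcomes do not include this question; it is a claim in the Discussion.
- *The second tier was meant to show what local staff can do entirely alone.* The article says only that they use existing resources.
- *Early workshop attendance raises the follow-up sites' baseline and biases their before-and-after change.* The article states no site-specific second-tier start date and no before-and-after analysis around one. Chat invitations go to providers already participating, so only voluntary workshop attendance could clearly come first. The effect is possible but not shown.
- *The sustainability claim must be withdrawn.* It is offered in addition to the 12-month period, and the limitations paragraph explains it as training local advocates and trainers. It needs qualifying, not removing.

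**Conclusion.** The point holds as a mismatch between a stated conclusion and the intervention as described. The Discussion's statement about local staff using existing resources would not follow from a rise at the seven follow-up sites, because such a rise would reflect local trainers together with research-led workshops and chat support. For the same reason, second-tier results within the 24-month period show spread with support; they do not show persistence after support ends.

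The reach can be stated, but not the size of any distortion. By design the chat invitation extends to participating providers at all seven follow-up sites. Workshop uptake is voluntary, and the article gives no figure from which to estimate it. The point rests on two assumptions: that at least some follow-up-site staff take up one of these offers, and that both count as study resources. The primary outcome at the five initial sites is not affected. The change is worth making but is not critical to the trial.

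**What to change.** 1. **Restate the claim.** In the Discussion, describe the second-tier result as the effect of a lower-intensity package: local trainers plus research-team workshops and chat support. In Intervention components, add that second-tier results within the 24-month period are read as supported spread, and that persistence is judged in the 12-month sustainability period.
2. **Log exposure by site.** Within the activity records already planned, record for each follow-up site the dates of first attendance at a research-led workshop, first chat-group membership and first train-the-trainer contact. Treat the earliest of the three as the start of exposure in any time-series analysis or comparison of intervention with non-intervention sites. Chat membership must count as study input alongside workshops.
3. **Report descriptively.** Show second-tier results according to whether staff had direct research-team training, without a formal comparison. Sites choose whether to attend and there are only seven, so motivation and training cannot be disentangled.

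The cost is a narrower claim for the second tier and one or two added log fields. No training or support is withheld from any site.
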